## Abstract

In the Diabetes Prevention Program (DPP) randomized, controlled clinical trial, participants who were  ≥ 60 years of age in the intensive lifestyle (diet and physical activity) intervention had a 71% reduction in incident diabetes over the 3-year trial. However, few of the 26.4 million American adults age ≥65 years with prediabetes are participating in the National DPP. The BRInging the Diabetes prevention program to GEriatric Populations (BRIDGE) randomized trial compares an in-person DPP program Tailored for Older AdulTs (DPP-TOAT) to a DPP-TOAT delivered via group virtual sessions (V-DPP-TOAT) in a randomized, controlled trial design (*N* = 230). Eligible patients are recruited through electronic health records (EHRs) and randomized to the DPP-TOAT or V-DPP-TOAT arm. The primary effectiveness outcome is 6-month weight loss and the primary implementation outcome is intervention session attendance with a non-inferiority design. Findings will inform best practices in the delivery of an evidence-based intervention.

## 1. Introduction

Over one-quarter (29.2%) of US adults aged 65 and older have Type 2 diabetes (i.e., 15.9 million people), and the Centers for Disease Control and Prevention (CDC) estimated that an additional 26.4 million older adults had prediabetes, defined as fasting plasma glucose values of 100 to 125 mg/dl or hemoglobin A1C values of 5.7 to 6.4%, in 2019 (1). Evidence-based diabetes prevention strategies, such as the National Diabetes Prevention Program (DPP), reduce the risk of developing diabetes but remain underutilized. In the original Diabetes Prevention Program (DPP) study, the diet and physical activity intervention conferred a 71% reduction in risk of type 2 diabetes for the participants who were ≥60 years of age (*n* = 648) after 3 years of follow-up (2). Since the seminal DPP was established as efficacious (2), the intervention has been implemented in hospital, community, work, and other settings.

Despite this, just 14.6% of rural counties and 48.4% of urban counties in the nation have a DPP site. Barriers to DPP participation exist for both individuals and healthcare systems. Individuals face barriers to access, including travel to 22 in-person sessions, as well as cost if they elect to utilize a commercial online program. Older adults, in particular, face barriers to care, including transportation, costs, time burden, and limited physical function/reserve. Healthcare systems face significant cost burdens for training DPP facilitators and hosting the program (3). In the few studies that have reported on costs of administering the DPP, there was a 5-fold difference in cost per participant across studies, with a virtual program costing less than on-site delivery (4, 5). In the BRInging the Diabetes prevention program to GEriatric Populations (BRIDGE) trial, we will address these barriers by generating a DPP Tailored for Older Adults (DPP-TOAT) and delivered via Virtual sessions (V-DPP-TOAT).

Technology use among older adults is increasing. Almost two-thirds (63%) of adults aged 66–75 years use the Internet to access health information, including 49% of adults aged 75 and older (6). Furthermore, 69% of adults ≥65 have a mobile phone, including 56% of adults ≥75 years of age. Web-based interventions have effectively increased health knowledge (7) and physical activity among older adults (8–10). The proportion of older adults enrolling in internet-based programs will grow with the aging of younger cohorts who are more accustomed to depending on technology to meet their health care and other needs.

Delivering a DPP through a videoconferencing platform may extend the program’s reach into the older adult community that may otherwise lack access (11). The NYU Langone Health catchment area includes more than 7.2 million people, of whom nearly 1 million individuals are aged 65 and older. An intervention using technology to provide remote training and individualized feedback increases the likelihood of reproducibility outside of the NYU Langone Health network and sustainability over time (12). Virtual interventions do not require brick-and-mortar facilities or centralized staff; these highly scalable interventions can be delivered from any location. However, a recent behavioral weight loss trial reported that in-clinic group visits, but not telephone group visits, resulted in statistically significant greater weight loss at 24  months compared with traditional in-clinic individual visits (13). Lessons learned from the implementation evaluation of the BRIDGE DPP will provide the opportunity for other healthcare systems to offer the program to eligible patients. The study aims are to compare the effectiveness and implementation of V-DPP-TOAT versus DPP-TOAT within a large healthcare system.

## 2. Methods

### 2.1. Study design and overview

We will conduct a type 1 hybrid (14), randomized, controlled trial of the BRInging the Diabetes prevention program to GEriatric Populations (BRIDGE) study, which will compare an in-person DPP Tailored for Older AdulTs (DPP-TOAT) to a DPP-TOAT delivered via group virtual sessions (V-DPP-TOAT; Figure 1). All randomized individuals (*N* = 230; 1:1 randomization) will receive 22 intervention sessions over the course of a year facilitated by a certified DPP lifestyle coach, but the delivery method will vary (virtual versus in-person).

**Figure 1 fig1:**
[figure not shown]
Study flow diagram.

Outcome assessments will be conducted at 0, 6, and 12 months at the clinic where we will assess weight, hemoglobin A1c, diet, and physical activity in both groups. At baseline, we will assess height, weight, waist circumference, and administer questionnaires to all participants. The trial design will adhere to the CONSORT checklist (see Appendix A), including an intention-to-treat analysis (15). Meticulous adherence to the study protocol and fidelity monitoring will ensure robust and unbiased results.

### 2.2. Recruitment

The NYU Langone Health patient population includes over 15,000 patients aged 65 or older with a diagnosis of prediabetes who meet the basic inclusion criteria. NYU Langone Health clinical providers utilize Epic, one of the country’s largest electronic health record platforms, and its patient portal (*MyChart*), which allows for direct outreach and bi-directional communication with patients. Using Epic, we will continuously identify eligible older adults with prediabetes. As in our prior work (16–19), patients will be recruited through both physician referral and proactive outreach to patients. For proactive outreach, we use Epic-generated lists of eligible patients based on our eligibility criteria. A research team member will send lists to patients’ primary care provider (PCP), who will subsequently identify any contraindications to participating. Potential participants will be sent a message through the patient portal (*MyChart*) and/or mailed a letter signed by the principal investigators (JB and JC) and medical director (EG) that describes the study and gives them the opportunity to opt out (i.e., request not to be contacted). We will then call potential participants to recruit, screen for eligibility, and schedule a baseline visit. Table 1 outlines eligibility criteria for study participation.

**Table 1 tab1:** Eligibility criteria.

Inclusion Criteria
• Aged ≥65 years*
• Prediabetes (A1C 5.7–6.4%, fasting glucose 100–125 mg/dl, or oral glucose tolerance test of 140–199 mg/dl within 12 mo) *
• BMI of ≥25 kg/m^2^, ≥ 23 kg/m^2^ if Asian American*
• English speaking*
• Under the care of PCP in the NYU Langone Health system*
• Able to travel to NYU medical center for in-person evaluations *
Exclusion Criteria
• Prevalent diabetes or End-Stage Renal Disease (> = CKD stage 3)*^±^
• Prior participation in Diabetes Prevention Program^±^
• A documented history of active psychosis or other cognitive issues via ICD-10 codes*
• Taking FDA-approved weight loss medications*^±^
• PCP stating that patient should not participate
• Inability to communicate due to severe, uncorrectable hearing loss or speech disorder^±^
• Severe visual impairment (if it precludes completion of assessments and/or intervention)^±^

*if assessed through EPIC, ±if assessed during screening. A1c, hemoglobin A1c; BMI, body mass index; mo, months; PCP, primary care provider; FDA, Food and Drug Administration.

#### 2.2.1. Randomization into Intervention Arms

The study statistician (HZ), will generate randomized treatment allocation in a blinded environment using a Research Electronic Data Capture (REDCap, https://projectredcap.org/) randomization tool.

#### 2.2.2. Retention

We will use the following strategies to encourage retention of participants in both arms of the study: (1) reminder of study visits and intervention sessions via email and phone call, (2) financial incentives following successful completion of study visits ($50 gift card for each baseline, 6, 12 month visits), (3) birthday cards, (4) certificates of completion and milestone emails.

#### 2.2.3. Masking

As with most behavioral trials, it is difficult to mask participants to the intervention arm. To reduce bias, all outcome assessors will be masked to the intervention arm and participants will be asked not to disclose treatment allocation. To detect potential unmasking, we will ask outcome assessors about participant allocation after each post-randomization measurement visit.

### 2.3. Intervention arms

#### 2.3.1. Common components to both interventions: V-DPP-TOAT and DPP-TOAT

Both programs will be composed of sixteen 60-min weekly/bi-weekly sessions followed by six 60-min monthly support sessions (see Appendix B) with a group size of 8–15 facilitated by a certified DPP lifestyle coach. The DPP intervention is based on Social Cognitive Theory (20), which focuses on the role played by self-referent thought in the maintenance of behavior change. The following describes the theoretical concepts threaded throughout the intervention sessions. Self-efficacy (e.g., the participant’s confidence in their ability to engage in healthier behavior) is derived from four major sources of information: (1) mastery experiences; (2) social modeling; (3) verbal persuasion; and (4) physiological states. Mastery experiences emphasize past successes; setting incremental, easily achievable goals; identifying modifiable barriers to healthy behavior; receiving positive feedback on goal achievement; and practicing problem solving skills around barriers to adherence. Social modeling enhances mastery when participants share their successes and help each other problem-solve around barriers they encounter. Verbal persuasion emphasizes the participant’s previous successes to demonstrate their capability (e.g., “As a result of your effort, you lost a pound last week. You can do it again.”) We will assist participants in recognizing physiologic benefits they experience from lifestyle change (e.g., more energy, better sleep, or BP control). Intervention materials, which are based on the 2021 PreventT2 lifestyle change program (21), will include:*Participant Manual*: An evidence-based manual describing detailed program content and personalized calorie and macronutrient recommendations to achieve the desired weight. Written at the sixth-grade reading level in a large (14 point) sans serif font, self-assessments and goal setting procedures will be included along with approaches to self-monitor food intake, physical activity, and cooking and meal pattern guides. To enhance self-identification with the program and for ongoing visual cues for program affiliation, we will provide tote bags inscribed with the institutional logo.*Tailoring of content for aging*: Based on our prior work (22), we have adapted group sessions to the unique needs of older adults. Resources include healthful eating strategies for dentition issues, changes in taste, and special attention to interactions between food and medications. Physical activity sessions provide adaptations for physical limitations, including chair exercises and strength training.*Food Guide*: Resources developed by the United States Department of Agriculture (23) providing tailored advice for older adults will be provided, along with instructions and tips for using programs such as Healthwatch 360 (24) to track calorie and nutrient intake compared to recommendations.*Hearing Assistance*: For participants in the in-person arm, we will offer a personal amplifier (PA; PockeTalker™) to all participants to address any self-reported or suspected hearing loss. A simple PA consists of an amplifier and microphone with the amplifier feeding a speaker’s voice directly into the wearer’s ears via headphones or ear buds. These devices reduce the difficulty with hearing in “difficult listening situations” by feeding the speaker’s amplified voice directly into the patient’s ear, while headphones or ear buds muffle external sounds (i.e., signal is louder than background noise level). These devices require no professional customization; simple volume and tuning controls allow for use directly out of the box. PAs enhance communication for those who have hearing loss in a variety of clinical settings (25–27). PAs were equivalent in performance to hearing aids in one randomized controlled trial (28), sound quality of PAs was preferred over hearing aids, improved physician-patient communication for elderly hospitalized patients (29) and understanding discharge information in an Emergency Department setting (30). Participants in the virtual arm will be offered ear buds to address any self-reported or suspected hearing loss.*Videos*: Each intervention session will also feature educational and behavioral coaching videos developed by our team or reputable organizations such as the National Institutes Health and VA MOVE (Weight Management Program, supported by VA’s National Center for Health Promotion and Disease Prevention) (31). The videos last 3–5 min, and will be used to anchor the discussion. Videos will also be available on the study website for participants to review as they desire.*Smart Scales*: We will provide participants with a Renpho® (Joicom Corporation, Eastvale, CA) Smart Scale for Body Weight, Digital Bathroom Scale for self-monitoring purposes and to monitor weight given the possibility of disruptions in in-person study visits due to COVID-19 pandemic restrictions. Renpho® Scales will transmit weights to researchers automatically using BlueTooth technology and have been used in other weight management studies. A research assistant will instruct each participant during the baseline visit on using the scale to report weekly weights, providing written instructions as well as a phone number and email address to obtain technical support as needed.

##### 2.3.1.1. V-DPP-TOAT Arm specific information

Intervention sessions will take place via videoconference rather than in-person, and we will encourage participants to use their preferred device to connect with the group (e.g., tablet, computer, and smartphone). Participants will be offered a tablet computer if they do not have an electronic device they’d like to use to connect. A research assistant will orient each participant to the tablet during the baseline visit, providing written instructions, a phone number and email address to obtain technical support as needed. Before or after the intervention session, participants will be assigned to breakout rooms where they will have a 1-on-1 visit with the lifestyle coach, report their weight, physical activity minutes and discuss action plan and goal achievement.

##### 2.3.1.2. DPP-TOAT Arm specific information

All interactions will be in-person and weights will be measured immediately before or after intervention sessions using a Renpho® scale.

### 2.4. Data collection

In-person data collection will occur during study visits for both arms. Assessments will occur at: baseline (first in-person encounter), six, and 12 months (Tables 2, 3). Participants will meet with a research assistant masked to treatment assignment to complete surveys and to measure glycemia, weight, height, and waist circumference (baseline, six, and 12 months). Research staff will administer all surveys, entering data directly into a REDCap database. The DPP facilitator will record DPP attendance data.

**Table 2 tab2:** Aim 1 BRIDGE measures.

Measures	Month			0	6	12
Demographics, health-related characteristics^1^^,^^2^^,^^3^	X		
Anthropometrics (height, weight, waist circumference)^4^	X	X	X
Hemoglobin A1c^5^	X	X	X
Social support^6^	X	X	X
Self-efficacy^7^	X	X	X
Dietary intake including alcohol, Food records (4 days including weekend day)	X	X	X
Physical activity record	X	X	X
Physical activity/sleep, accelerometry	X	X	X
Smoking^8^	X	X	X
Quality of life^9^^,^^10^	X	X	X
Physical function, walking limitations^11^	X	X	X

1 Prediabetes Risk Test (32).

2 Health literacy (33, 34).

3 Technology use (35).

4 Anthropometric measures (36).

5 Blood draw per standard HbA1c protocol.

6 NIH adult toolbox social relationship scales (37).

7 Weight efficacy lifestyle questionnaire (38).

8 Smoking (39).

9 Emotional wellbeing (40).

10 Summary score (40).

11 Physical functioning (40).

**Table 3 tab3:** Aim 2 BRIDGE measures.

		Month		
Component		0	6	12
R	Recruitment^1^^,^^2^^,^^3^	X		
E	Weight and HbA1c outcomes^4^	X	X	X
A	Adoption by the healthcare system^5^		X	X
	Fidelity to CDC DPP curriculum^6^		X	X
I	Participant attendance at group sessions^7^		X	X
	Participant and DPP facilitator acceptability^8^		X	X
	Cost analysis^9^			X
M	Weight and HbA1c outcomes^4^			X
	Program maintenance and growth^5^			X

RE-AIM, reach, efficacy, adoption, implementation, maintenance; HbA1c, hemoglobin A1c; CDC, Centers for Disease Control and Prevention; DPP, diabetes prevention program.

1 Use EPIC to evaluate the number (proportion) of individuals who are:

a Eligible for the study based on EHR data.

b Invited to participate through MyChart and/or via study recruitment mailings.

c Responsive to study invitation.

d Enrolled in study.

2 Evaluate factors associated with participation by comparing the demographic and clinical characteristics of patients reached by the intervention vs. those not reached.

3 Evaluate reasons for not participating (one multiple choice question at end of screening).

4 Outcomes assessment per standardized procedures (see aim 1 measures table).

5 Intervention process data and key informant interviews.

6 Training Period – Monitor skill acquisition and quality of counseling.

• Lifestyle coaches completed CDC training via New York City Department of Health.

• Curriculum certification requirements are built into data collection (e.g., attendance, weekly weigh-ins, physical activity minute tracking).

• Intervention Period – Record group sessions throughout the intervention period, and a study team member will monitor 10% of the sessions.

o Fidelity Checklist.

o Will provide refresher training if fidelity checklist ratings average < 80%.

7 Measure attendance, outcomes assessment completion, and diet and physical activity monitoring completion.

8 Acceptability and Feasibility.

9 Costs associated with staffing, supplies, and participant time for each arm.

#### 2.4.1. Aim 1: to evaluate the effectiveness of the V-DPP-TOAT compared to the DPP-TOAT

Core measures for Aim 1 are displayed in Table 2.

#### 2.4.2. Aim 1: quantitative data analysis

We will compare the effect of the V-DPP-TOAT versus the DPP-TOAT interventions on weight and glycemia, which are both continuous outcomes. First, we will report means and standard deviations by randomization assignment and assess the assumption of normality in the outcomes. We will estimate the model using ordinary least squares regression
$$Y6_{i}=\beta_{0}+\alpha_{0}Y0_{i}+\alpha_{1}P_{i}+e_{i}$$
where 
$Y6_{i}$
 is the 6-month weight or Hemoglobin A1c for participant 
i
. 
$Y0_{i}$
 is the baseline weight or A1c for participant 
i
. 
$P_{i}$
 is an indicator variable, where 
$P_{i}=1$
 if the participant 
i
 has been randomized to V-DPP-TOAT, and 
$P_{i}=0$
 for the DPP-TOAT. 
$e_{i}$
 is an error term. The parameters to be estimated are as follows: 
$\beta_{0}$
 is the average for those in the DPP-TOAT group; 
$\alpha_{0}$
 represents the relationship between the baseline and follow-up outcome (weight or A1c) measurement; if the relationship is strong, the inclusion of the baseline measurement can increase statistical power; and 
$\alpha_{1}$
 represents the effect of the V-DPP-TOAT intervention. Specifically, the hypothesis test will compare 
$H_{0}:\alpha_{1}<\Delta$
 vs. 
$H_{A}:\alpha_{1}\geq -\Delta$
 with the noninferiority margin 
Δ
 set as 5% for each of the outcomes. We will calculate the 95% confidence interval of 
$\alpha_{1}$
. If the lower bound is above the margin -Δ, the V-DPP-TOAT is deemed non-inferior and the trial is a “success.” Further, if the lower bound of that same CI is also above zero, then superiority of V-DPP-TOAT can also be declared (41). Interaction terms between 
$Y0_{i}$
 and 
$P_{i}$
 will be tested to see if there is effect modification by any of the baseline covariates.

We will assess heterogeneity in outcomes among healthcare settings/clinics by estimating an intraclass correlation coefficient (ICC). If the heterogeneity cannot be ignored, we will use a multi-level model with nested random effects in the above equation to accommodate the correlations caused by healthcare settings/centers. Outcomes analysis will use an intention-to-treat principle, with a per-protocol analysis as a sensitivity analysis (41) employing R software (version 1.2.5019, R Foundation for Statistical Computing) for all analyses.

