##### 2.4.2.1. Sensitivity analysis for missing data

We will compare demographic and clinical covariates in participants with and without missing data to identify factors potentially contributing to missingness. We will use 10 multiple imputations from the original dataset using the predictive mean matching method substituting missing values within each impute.

##### 2.4.2.2. Power: aim 1

To achieve 80% power to detect non-inferiority using a one-sided, two-sample *t*-test (lower bound), we will need 85 participants per group. The margin of non-inferiority is 5% of weight loss in the DPP-TOAT arm. The true efficacy difference between the 6-month weight loss is assumed to be 1.6 kg (weight loss of 5 kg in the V-DPP-TOAT arm and 6.6 kg in the in-person DPP-TOAT arm with standard deviation of 5 kg in each arm (42)). The significance level (alpha) of the test is 0.05. A total of 230 participants are needed, assuming 25% attrition at 6 months based on data from our work and others (22, 42, 43).

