Block, 2015 (54, 55)	Randomized, controlled trial	339	Recruited from Palo Alto Medical Foundation; Mean age 55.0 (8.9)	Alive PD-1-year program of regular contact and goal setting, weekly in the first 6 months and biweekly thereafter, plus midweek automated email and mobile phone	Automated online platform with interactive voice response phone calls and a mobile app.	Alive-PD participants achieved significantly greater reductions than controls in fasting glucose (mean − 7.36 vs. −2.19 mg/dl, *p* < 0.001), HbA1c (mean − 0.26%vs. mean − 0.18% *p* < 0.001), and body w eight (mean − 3.3 vs. −1.3 kg, *p* < 0.001).
Castro Sweet, 2018 (46)	Single-arm, retrospective	501	Humana Medicare Advantage beneficiaries with evidence of prediabetes/metabolic syndrome	Prevent – a DPP-based group lifestyle intervention that integrates a private online social network, weekly lessons, health coaching, and a w ireless scale and pedometer. Consists of a core 16-w eek intensive lifestyle change intervention and post-core lifestyle change maintenance intervention	Online platform, mobile app	92% completed at least 9 of 16 core lessons. At 12 months, average weight loss was 7.5% (7.8). Among participants with clinical data, average HbA1c decrease was 0.14% (*p* = 0.001) and average total cholesterol decrease was 7.08 mg/dl (*p* = 0.008). Self-reported w ell-being, depression, and self-care improved (*p* < 0.0001).
Lee, 2018 (42)	*Post hoc* analysis of two prospective, pragmatic, nonrandomized studies	≥65 years: 120 <65 years: 258	Veterans with prediabetes	VA-DPP – DPP Group Lifestyle Balance curriculum’s 16 core sessions over 6 months followed by 6 monthly maintenance sessions Online-DPP – Prevent curriculum, weekly online modules over 12 months	VA-DPP: In-person Online-DPP: Online platform, mobile app	A higher proportion completed eight or more sessions in the Online-DPP intervention than in the VA-DPP intervention (*p* < 0.05). Veterans ≥65 years achieved similar participation and weight loss as younger adults, whether DPP was delivered in person or online. Both age groups lost a clinically and statistically significant amount of weight (5 kg or 5% weight at 6 and 12 months; *p* < 0.05) and had similar w eight loss trajectories over the 12 months (*p* < 0.05).

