Almeida, 2020/Katula, 2020 (56, 57)	Randomized, controlled trial	599	Nebraska Medicine primary care clinics	Omada Health Program – 16-week intensive curriculum focusing on w eight loss follow ed. by 36-week curriculum focusing on weight maintenance	Online platform, mobile app versus one two hour group diabetes prevention class	Omada produced significantly greater reductions in HbA1c (−0.23 vs. −0.15%, *p* < 0.01) and reduction in percent change of body w eight from initial w eight (−5.4 vs. −2.0%, *p* < 0.01) relative to control at 12 months.
Fitzpatrick 2021 (55)	Mixed-methods natural experiment	7,123	Kaiser Permanente Northwest patients	In-person DPP Digital DPP versus Omada Health Program compared	In-person versus online platform	In progress

DPP, diabetes prevention program; HbA1c, hemoglobin A1c; VA, veterans administration.

Our study has several strengths. The results of our trial can directly inform policy recommendations to Medicare that will have broad implications for older adults with prediabetes (63). Another major strength is our ability to recruit a diverse study population from broad socioeconomic backgrounds, which will help us to better understand how implementation may need to be tailored for different populations and settings. Our team has the breadth and depth of experience in conducting behavioral intervention trials and implementation to analyze results and interpret them for stakeholders to inform potential future adoption of the DPP by a large healthcare system. We have also identified several challenges and discussed ways to address these. First, trials often have challenges recruiting people from underrepresented groups. Our experience recruiting underserved populations from health care systems enhances our ability to meet recruitment targets. Second, there is inherent measurement error associated with self-reported dietary intake, but we do not expect the measurement error to differ between randomized groups, allowing for a valid, randomized comparison. Third, though using technology to engage participants can be challenging, technology use among older adults is increasing (64), and our prior and ongoing work suggests it is feasible and increases opportunities for broader dissemination of successful interventions.

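### The 5% HbA1c non-inferiority margin has no stated base: as 5% of the level (0.29–0.32 points) it exceeds every HbA1c reduction in Table 4; as 5% of the reduction (about 0.01) it is unattainable

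*Protocol article*

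**What the plan says.** Section 2.4.2 fits one regression to each of two outcomes, weight and glycaemia. The dependent variable "is the 6-month weight or Hemoglobin A1c for participant" i, adjusted for the baseline value, so the outcome modelled is the level at 6 months and not the change. The margin Δ is "set as 5% for each of the outcomes". The decision rule is common to both outcomes: "We will calculate the 95% confidence interval of" the treatment coefficient, and then "If the lower bound is above the margin -Δ, the V-DPP-TOAT is deemed non-inferior and the trial is a “success". No margin in HbA1c units is given, and no base for the percentage.

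The only place that names a base is Section 2.4.2.2 (Power: aim 1), which concerns weight alone: "The margin of non-inferiority is 5% of weight loss in the DPP-TOAT arm". That section gives no power or sample size for HbA1c.

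Two other places set the scale for HbA1c. Table 1 admits patients with "Prediabetes (A1C 5.7–6.4"%, or on fasting glucose or an oral glucose tolerance test. Table 4 lists HbA1c results from three programmes. The automated online programme trial has falls of 0.26 against 0.18. In the single-arm Medicare Advantage study the "average HbA1c decrease was 0.14"%. For the Nebraska primary care trial the table states "Omada produced significantly greater reductions in HbA1c (−0.23 vs. −0.15"%).

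The Abstract names 6-month weight loss as the primary effectiveness outcome. Section 2.4.3, under Maintenance, counts glycaemia among the primary clinical outcomes.

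**The concern.** A relative margin works very differently on the two scales. HbA1c in prediabetes sits in a narrow band, and programme effects are a few tenths of a point or less, so a small percentage of the level can be as large as the whole treatment effect. A non-inferiority claim would then not show that the virtual programme keeps any of the in-person benefit on glycaemia. A small percentage of the effect, on the other hand, is far below what a trial of this size can resolve. The same printed rule could therefore give an almost empty claim or an almost certain failure, depending on a choice that the article leaves open. The Discussion says that the results can inform Medicare policy, so a glycaemic non-inferiority statement would be read and used.

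**Working it through.** **The plan's own figure.** There is none to reproduce for HbA1c. The weight calculation (85 per group) does not settle which base is meant. With the margin as described in Section 2.4.2.2, 0.05 × 6.6 = 0.33 kg, and the virtual arm assumed worse by 6.6 − 5 = 1.6 kg, the assumed deficit exceeds the margin and no sample size gives 80% power. A figure near 85 appears if the sign of the 1.6 kg is reversed (83–84 per arm). It also appears if the margin is about 3.5 kg, which is 5% of an assumed body weight of 70 kg (86–87 per arm).

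**Inputs for HbA1c.**
- From the article: margin 5%; two-sided 95% CI; entry A1C 5.7–6.4%; programme-arm falls of 0.26, 0.23 and 0.14; comparator falls of 0.18 and 0.15; 230 randomised 1:1 with 25% attrition, so 115 × 0.75 ≈ 86 per arm.
- Assumed, because the article gives no value: SD of 6-month HbA1c (after baseline adjustment) 0.2 to 0.4 points.
- Assumed: the CI is read on the clinically correct side, so that a higher HbA1c in the virtual arm counts against it.

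**Reading A: 5% of the HbA1c level.**
- 0.05 × 5.7 = 0.285; 0.05 × 6.0 = 0.30; 0.05 × 6.4 = 0.32.
- Net effects in the two randomised trials: 0.26 − 0.18 = 0.08 and 0.23 − 0.15 = 0.08.
- Smallest margin against the reductions: 0.285/0.26 = 1.1; 0.285/0.23 = 1.2; 0.285/0.14 = 2.0.
- Against the net effect: 0.285/0.08 = 3.6, up to 0.32/0.08 = 4.0.
- Entry on glucose criteria may admit values below 5.7%, but the mean would have to be 0.26/0.05 = 5.2% or lower before the margin stopped exceeding the largest reduction.

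Probability that a virtual arm with no HbA1c change is declared non-inferior when the in-person arm falls by d:

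P = Φ((M − d)/SE − 1.96), with SE = SD × √(2/86) and M = 0.30. SE is 0.0305, 0.0457 and 0.0610 for SD 0.2, 0.3 and 0.4.

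| In-person fall d | SD 0.2 | SD 0.3 | SD 0.4 |
|---|---|---|---|
| 0.08 | >99% | >99% | 95% |
| 0.14 | >99% | 94% | 75% |
| 0.23 | 63% | 33% | 21% |
| 0.26 | 26% | 14% | 10% |

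Only the difference between the arms enters the formula. The 0.08 row therefore also describes a virtual arm that falls 0.08 less than the in-person arm, which is the gap between programme and comparator in both Table 4 trials.

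**Reading B: 5% of the in-person reduction**, by analogy with the weight wording in Section 2.4.2.2.
- 0.05 × 0.14 = 0.007; 0.05 × 0.26 = 0.013.
- Two truly identical arms (d = 0) pass with probability Φ(M/SE − 1.96). The lowest value is Φ(0.007/0.0610 − 1.96) = 3% and the highest is Φ(0.013/0.0305 − 1.96) = 6%.

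**The case against.** The strongest objection is that the article never says the HbA1c margin is about 0.3. A reader might infer that it is, and that a virtual programme with no glycaemic effect would almost certainly be declared non-inferior. The documents do not support that. Reading A is the more literal one for Section 2.4.2, because the level is what is modelled, but the only base stated anywhere is the control-arm change. On that base a virtual arm with no effect would practically never pass a correctly signed test. Even under Reading A, the result depends on the in-person effect: at falls of 0.23 or 0.26 a virtual arm with no change fails more often than not in most of the range examined. This part of the objection stands, and the point is therefore put as an undefined base with two unusable readings.

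A second objection also stands. The HbA1c results in Table 4 all come from online programmes. The completed in-person programme listed there is reported for participation and weight, not HbA1c. A reader might infer that the margin has to lie below 0.08, but that net effect is not an in-person effect and does not fix a limit for this trial.

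Third, the Abstract names weight as the primary effectiveness outcome and the trial is sized on weight, so it would be wrong to infer that the trial's main conclusion rests on the HbA1c margin. That limits the consequence but does not remove the point: Section 2.4.2 applies the margin and the success rule to each outcome explicitly. This is a printed decision rule, not a detail left to an analysis plan.

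Finally, the printed rule guards the wrong side for an outcome where lower is better. That is a separate defect. The probabilities above assume it has been corrected, and correcting it leaves this one in place.

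**Conclusion.** The concern holds in this form: the 5% HbA1c margin has no defined base, and neither reading that the article offers gives a usable non-inferiority test. As a share of the level it is 0.285–0.32 points for entry values of 5.7–6.4%, too wide to protect any HbA1c reduction shown in Table 4. As a share of the reduction it is roughly 0.01 points, which a trial of this size cannot demonstrate.

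The margin arithmetic needs only the article's figures. The pass probabilities also rest on the assumed SD of 0.2–0.4, on 86 per arm and on a correctly signed interval. How often an ineffective virtual arm would pass under the wide reading runs from about 10% to over 99% across the effects in Table 4. It cannot be narrowed further, because the article reports no HbA1c effect for an in-person programme.

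**What to change.** Take HbA1c out of the 5% non-inferiority and success rule in Section 2.4.2. Report the between-arm HbA1c difference as a secondary estimate with its 95% CI and no non-inferiority claim.

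If a non-inferiority claim on HbA1c is wanted, state a separate margin in HbA1c percentage points. Justify it by the in-person effect to be preserved, with the source of that effect, and say plainly that the trial is sized for weight only.

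The cost is wording in the protocol and analysis plan. Design, data collection and sample size do not change. Under the first option the sponsor gives up a glycaemic non-inferiority claim that the present margin could not support.
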